305 The patient level intervention consists of materials mailed to all individuals meeting eligibility criteria at  
306 intervention clinics. The materials include two components: 1) An informational brochure introducing the  
307 idea of discontinuing unnecessary or potentially inappropriate medications as part of optimal medication  
308 management. Based on an established model of patient-centered deprescribing and adapted from a direct-  
309 to-consumer deprescribing intervention targeting older adults on benzodiazepine medications, this brochure  
310 has been revised based on patient and care partner input. 2) A short (9 question), validated version of the  
311 revised Patients' Attitudes Towards Deprescribing (rPATD) questionnaire which captures the beliefs,  
312 attitudes and experiences of people about deprescribing. The mailing will include a stamped self-  
313 addressed envelope to return the rPATD questionnaire. A cover letter for the materials will provide general  
314 information about the study along with contact information for the principal investigators and project  
315 managers. Completing the rPATD questionnaire serves two purposes for the study: 1) Engaging patients in  
316 forming and answering questions is a known method of increasing patient engagement. Additionally, the  
317 response data will allow us to explore the effect of patient/care partner attitudes towards deprescribing on  
318 outcomes within intervention groups. Materials will encourage patients/ care partners to discuss any interest  
319 in deprescribing with their PCP at a primary care visit. The information specifically includes instructions  
320 NOT to discontinue any medications without talking to their PCP. Patient/care partner participants will  
321 receive materials within a 2-week period prior to a scheduled visit with their PCP. Patients will be eligible  
322 for up to two possible mailings if subsequent PCP visits are at least 2 months apart. We will send a second  
323 rPATD to patients who have not returned the rPATD from the initial mailing.

324 The clinician level intervention includes: 1) An initial 15- to 20-minute educational presentation at the  
325 clinic department (family medicine or internal medicine) monthly provider meeting focusing on  
326 deprescribing as one element of optimal medication management for ADRD individuals. 2) One-page paper  

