## 2.2 Study Enrollment Procedures

**Intervention recruitment plan.** Using EHR data and the KPCO Virtual Data Warehouse (VDW), a quality-controlled common data model derived from multiple KPCO data sources (EHR, membership, pharmacy, laboratory, and other clinical data), study personnel will identify eligible patients who receive primary care at the intervention and control clinics. At least weekly during the intervention period, study personnel will review the list of eligible participants to identify those at an intervention clinic with an appointment with their PCP 7 or more days in advance. Those with upcoming appointments will receive study materials and will be entered into a study database for tracking. Patients will be eligible to receive up to 2 mailings at least 8 weeks apart.

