## 4 STUDY PROCEDURES

### 4.1 Schedule of Evaluations for initial intervention

| Assessment                                                                     | Identify Eligible Population | Baseline, Enrollment, 2 weeks prior to scheduled visit | 6 months post brochure mailing | 12 months post brochure mailing |
|--------------------------------------------------------------------------------|------------------------------|--------------------------------------------------------|--------------------------------|---------------------------------|
| Inclusion/Exclusion Criteria                                                   | X                            |                                                        |                                |                                 |
| Demographics- age, gender, race, ethnicity                                     | X                            |                                                        |                                |                                 |
| Primary outcomes (Aim 1)                                                       |                              |                                                        |                                |                                 |
| Current Medications                                                            | X                            | X                                                      |                                |                                 |
| Number of Drugs                                                                | X                            | X                                                      | X                              | X                               |
| Percent of individuals with one or more Potentially Inappropriate Medications* | X                            | X                                                      | X                              | X                               |
| Secondary outcomes (Aim 2)                                                     |                              |                                                        |                                |                                 |
| Dose Reductions                                                                |                              |                                                        |                                | X                               |

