### 490 Definitions

of assessment variables from Schedule 4.1 above and associated data elements and sources are itemized

below. Unless otherwise mentioned, all data will be extracted from the KPCO Virtual Data Warehouse, a quality controlled, common data model that includes data from multiple KPCO data sources covering the following domains: Enrollment, utilization, pharmacy, tumor registry, demographics, lab results, mortality, vital signs, census data, geocoded demographic data, patient reported outcomes collected in the course of care, problem list diagnoses, and social history.

Inclusion/ exclusion criteria: as previously described. Data elements will include age, diagnosis codes, location of primary care provider, current medications. Chronic diagnoses will be from a list of 86 chronic conditions itemized in the Multiple Chronic Conditions Chartbook (Gerteis J, et al.). We have developed a method of counting chronic medications that utilizes the Generic Product Index (GPI) in a manner similar to prior work using the WHO Anatomic Therapeutic Chemical index A. Study experts ([name], [name], [name], [name], [name]) created a consensus-based list of GPI categories to be included in estimating the criterion of 5 or more chronic medications (this list excludes drug classes unlikely to be used as chronic medications, such as vaccines and anesthetics).

Demographics: age, gender, self-reported race/ethnicity from the EHR, census-based socioeconomic status.

Diagnoses: ICD-9 (historical) and ICD-10 codes will be used to identify diagnoses from visit billing codes, hospital and emergency department claims, and problem list diagnoses.

Current chronic medications: Total number of chronic medications on the date of study eligibility. Chronic medication use is defined as any medication for which the patient had at least a 28-day supply on the baseline eligibility date. We selected a 28-day supply (rather than a supply for a longer time period) because opioid medications are often dispensed in 28-day supplies. All current medications exclude the following domains identified by 2-digit GPI codes: Vaccines, Toxoids, Allergenic extracts, Oxytocics, Local anesthetics – parenteral, General anesthetics, Antiseptics and disinfectants, Antidotes, Diagnostic products, Chemicals, and Medical devices.

Primary Outcomes:

Number of drugs: number of chronic medications – see above.

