Percent of individuals taking one or more PIMs: chronic medications that are listed as potentially inappropriate for older adults based on the Beers list plus opioid medications.

520 Secondary Outcomes:

521 Dose reductions: Because calculating dose reductions requires analyzing specific targeted medications, we  
522 will assess dose reductions in three selected drug classes. We selected these classes based on the premise  
523 that the medications posed risks of adverse side effects, but that patients, care partners, and clinicians may  
524 be reluctant to discontinue the medications for fear of recurrent symptoms. The three drug classes are  
525 benzodiazepines, opiates, and antipsychotics.

526 Adverse Drug Events: We will examine three types of ADEs that are common causes of emergency service  
527 use among older adults and that may plausibly be expected to decrease in a culture of thoughtful  
528 deprescribing. These are falls; hemorrhagic events; and episodes of hypoglycemia in individuals with  
529 diabetes. All of these outcomes will be calculated from ICD-10 diagnoses using code lists extracted from  
530 the literature and/or previously validated at KPCO. Rates will be calculated for the year prior to baseline  
531 and the year following the initial brochure mailing. Denominators will use person-years to account for  
532 changes in enrollment and deaths.

533 ADLs: Activities of Daily Living are reported by patients/ proxy responders as part of the annual Medicare  
534 Health Risk Assessment (HRA). These data will be available on the subset of patient participants who have  
535 completed the HRA. (Estimated at 45% of the KPCO Medicare beneficiary population.) Data from the most  
536 recent HRA will be used.

537 Hospitalization rate, emergency department visit rate, skilled nursing facility admission rate: Presence/  
538 absence of a one of these admissions over the year prior to baseline and post intervention. (We will  
539 distinguish between temporary and permanent admissions to skilled nursing facilities.)

540 Mortality: Death from any cause during the study period.

541 Additional planned evaluations:

542 Following the intervention, we will explore mechanisms of intervention effectiveness and uptake through  
543 post hoc qualitative interviews with patients, family caregivers, and clinicians; patient and clinician survey  
544 responses; and descriptions of outpatient office visit length. Data and variables include:

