rPATD: revised Patients' Attitudes Towards Deprescribing 9-question questionnaire and one question on who completed it. Collected from patients/ care partners as part of the intervention on paper and returned by mail.

PPMD: Physicians Perception of Medication Discontinuation. Collected on paper during the initial portion of the clinician intervention – presentation at clinician team meeting.

Physician specialty: Will be obtained from Colorado Permanente Medical Group data sources.

Time and interval definitions: Enrollment, Baseline, and/or Randomization:

Baseline: The baseline point will be defined as the time at which patients are identified as having an upcoming appointment with their PCP and are mailed the intervention materials. For patients who receive second mailings in advance of a subsequent PCP visit, baseline will remain their first visit but second mailings will be tracked and examined in selected analyses. Baseline for patients in the control clinics will be the date of the first PCP appointment during the initial intervention period. Identical methods will be used to screen control patients for eligibility and identify upcoming visits as described above to ensure comparable identification.

Randomization: Randomization will be at the clinic level and will be stratified by clinic size. (See analytic plan below.)

Follow-up Visits: Data extractions do not depend on follow up visits in this study. Dates for follow up measurements described in the Evaluations Table will be relative to baseline and data will be extracted from the VDW as described above.

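### Baseline is the identification and mailing date in intervention clinics but the appointment date in control clinics, so time zero depends on the arm

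*Protocol*

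**What the plan says.** The rule is in the time and interval definitions of Protocol section 4.2.

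- **Intervention clinics:** baseline is when patients are "identified as having an upcoming appointment with their PCP and are mailed the intervention materials".
- **Control clinics:** "Baseline for patients in the control clinics will be the date of the first PCP appointment during the initial intervention period".
- **Second mailings:** the sentence on intervention patients mailed twice says their baseline stays at the first visit, although the sentence before it set baseline at the mailing.
- **Screening:** control patients are screened for eligibility and upcoming visits in the same way as intervention patients. This sentence sets no date.
- **Follow-up:** "Dates for follow up measurements described in the Evaluations Table will be relative to baseline".

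Other sections bear on the gap between the two anchors. Section 2.2 selects patients with an "appointment with their PCP 7 or more days in advance", and the Précis gives the same minimum for mailing. Section 2, in the text under the timeline, says patients will "receive materials within a 2-week period prior to a scheduled visit with their PCP". The section 4.1 schedule has a single baseline column, labelled two weeks before the scheduled visit, and its follow-up columns count from the mailing ("6 months post brochure mailing"). The adverse drug event definition in section 4.2 uses the year before baseline "and the year following the initial brochure mailing".

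**The concern.** Section 7.5 estimates the effect as an intervention-by-time interaction, with adjustment for baseline medication use. That comparison needs baseline to mean the same event in both arms. Randomizing clinics balances patients; it does not remove a date rule that differs by arm.

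The visit matters because it is where the mailed materials are meant to prompt a discussion of deprescribing. With the rule as written, it falls inside follow-up for intervention patients and on day zero for control patients. Three things could follow:

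- Follow-up measurements are taken at different distances from the visit.
- Events in the days before the visit count as follow-up in one arm and as history in the other.
- A prescription filled on the visit day could count in the baseline of control patients only. This would affect both primary outcomes, the medication count and the proportion on a potentially inappropriate medication.

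The brochure-mailing anchor in section 4.1 and in the adverse drug event definition also has no counterpart in control clinics, where nothing was mailed.

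**Working it through.** The protocol states no figure that depends on the baseline date, so there is none to reproduce. The check is to infer the offset and then trace where it goes.

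**1. Offset between the two anchors.** Section 2.2 and the Précis give a minimum lead of 7 days. Section 2 has the materials arriving in the two weeks before the visit, and the section 4.1 baseline column says two weeks. Together these suggest about 7 to 14 days. This is an inference from a minimum lead, a receipt window and a column label.

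**2. Offset as a share of follow-up** (6 months = 183 days, 12 months = 365 days):

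- 6 months: 7/183 = 3.8%; 14/183 = 7.7%.
- 12 months: 7/365 = 1.9%; 14/365 = 3.8%.

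**3. Distance from index visit to measurement.**

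- 6 months: 183 − 14 = 169 to 183 − 7 = 176 days in the intervention arm, against 183 in control.
- 12 months: 365 − 14 = 351 to 365 − 7 = 358 days, against 365.

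**4. Event windows.** Section 5.3 anticipates hospitalization of up to 30%, read here as annual. Section 7.2 gives 3,671 eligible members; half per arm is assumed, about 1,835.

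- Expected in 7 days: 1,835 × 0.30 × 7/365 ≈ 11.
- Expected in 14 days: 1,835 × 0.30 × 14/365 ≈ 21.

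These events, 0.6-1.1% of the arm, count as follow-up in intervention clinics. In control clinics the same days before the visit count as history. The windows are shifted, not shortened: control patients gain the same number of days at the far end. The 11 to 21 are therefore events classified differently, not a net excess in one arm.

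**5. Visit-day dispensing.** Let *s* be the mean rise in the medication count from prescriptions filled on the visit day.

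- If *s* enters the control baseline only, the control group appears to fall by *s* more than it did.
- In a pure difference-in-change model the estimate is biased by *s* against the intervention. With baseline as a covariate of slope *b*, the bias is *b* × *s*. Section 7.5 mentions both elements.
- The protocol gives neither *s* nor *b*, and does not say whether visit-day fills count. Its rule is that the patient "had at least a 28-day supply on the baseline eligibility date", without tying that date to either anchor.
- Purely as an assumption, *s* from 0 to 0.20 medicines would be 0 to 0.20/0.70 = 29% of the 0.70 difference in section 7.2. With an assumed *b* of 0.8 the top of the range is 0.16/0.70 = 23%. Nothing in the document favours any value in these ranges.

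**6. Power.** The inputs in section 7.2 (3,671 members, 18 clinics, rate 6.8, ICC 0.01) do not use the baseline date, so the date rule leaves the plan's power calculation unchanged.

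**The case against.** The strongest reply is that the paragraph itself treats the first visit as the intervention baseline, in the clause on second mailings. On that reading the anchors coincide and the offset is about zero. The clause is real, and it means the offset cannot be called certain. But it concerns which of two contacts counts, and it contradicts the explicit definition just before it. It leaves the intervention anchor inconsistent; it does not make the rule common to both arms.

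A second reply is that 7 to 14 days appears nowhere as an interval between baseline dates. That stands. Section 2.2 sets no maximum lead, and section 2 speaks of receipt, not posting, so the true gap could be shorter or longer.

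Third, the medication bias may not exist. Section 4.2 counts medicines on the eligibility date, and the section 4.1 schedule has a separate column for identifying the eligible population in which medication counts and inappropriate medications are already recorded. If that count serves as baseline, visit-day fills never enter it. This also stands.

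Fourth, the mailing anchor in the schedule is partly cured by section 4.2, which makes the schedule's follow-up dates relative to baseline. Agreed for the schedule; the adverse drug event window is not cured.

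Finally, a common anchor was probably intended. Control patients are screened identically, and sections 5.2 and 7.3 define the safety comparison group by the mailing they would have been eligible for. Those sections define a group, however, not a date.

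A reader might go further and infer a proven bias of a given size, or a loss of power. The document supports neither: any size rests on an assumed *s*, and the power inputs do not involve the date rule.

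**Conclusion.** The point holds as a defect in the date rule. The protocol names a different baseline event for each arm, and it is inconsistent about the intervention event. This is a rule fixed badly, not detail left for an analysis plan.

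Read literally, the arms are offset by an inferred 1 to 2 weeks, about 4-8% of the 6-month and 2-4% of the 12-month interval, and follow-up dates and event windows move with it. A shift of that length in a chronic medication count need not matter much.

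The baseline-count bias is conditional on visit-day dispensing being counted. It would run against the intervention if dispensing rises at the visit, and it may be small or nil. The point is worth correcting because the rule differs by arm and is cheap to align, not because a material distortion has been shown.

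**What to change.** 1. In section 4.2, define control baseline as the date the patient would have been identified and mailed under the same weekly screen used in intervention clinics (appointment at least 7 days ahead).
2. In the same paragraph, reword the second-mailing clause so that an intervention patient's baseline stays at the date of the first mailing.
3. In the section 4.1 follow-up columns and the adverse drug event definition in section 4.2, count from baseline instead of from the brochure mailing, for both arms.

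The mailing date is a better common anchor than the visit, because in intervention clinics the visit comes after the materials have gone out.

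The cost is one redefined sentence, matching edits in three places and one date variable in the control extraction. The date should be derivable, since control patients are already screened in the same way and those who would have been mailed are already identified for safety monitoring. The offset in the date rule then falls to zero, with no added patients or data collection and no change to the power inputs.

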## **5 SAFETY ASSESSMENTS**

Safety Monitoring processes were developed in conjunction with the NIA, and the study Data Safety Monitoring Board (DSMB).

## **5.1 Specification of Safety Parameters**

The intervention is educational for both patients / care partners and clinicians and does not in itself actively deprescribe medications. The decision and process for deprescribing is left to the PCP in shared decision making with the patient and his or her care partners.

There is still the potential for adverse effects or unintended consequences from the intervention including: inadvertent stopping of necessary medications by patients or care partners and associated effects of those potential discontinuations, longer patient – PCP visit encounters devoted to medication discussions or clarifying misunderstandings, and lower satisfaction of patients/ care partners about medication management. If PCPs and patient/ care partners elect to discontinue specific medications, there is the potential for recurrent symptoms, adverse drug withdrawal events, and anxiety about the deprescribing process. Potential risks can be minimized or prevented by using a patient-centered, physician-led, structured deprescribing process.

## **5.2 Methods and Timing for Assessing, Recording, and Analyzing Safety Parameters**

There are two primary elements to the safety monitoring plan: comparing rates of potential serious adverse events between intervention and control clinics; and chart abstractions of a sample of patients who experience a potential serious adverse event in each group.

Comparing rates of potential serious adverse events: Every 3 months rates of hospitalizations, and mortality will be compared between groups who have received the intervention (have been sent a mailing) from intervention clinics, and those who would have been eligible to receive the initial mailing from control clinics. These rates will be reported to the DSMB at usual meetings. Chart Abstractions: These will be conducted on all deaths and a sample of every third hospitalization to determine if the potential serious adverse event occurred within 4 months of a medication adjustment by the patient’s primary care physician. Causality related to the medication adjustment will be reviewed in a blinded fashion by steering committee investigators ([name], [name], [name]). Findings will be reported to the DSMB at usual meetings. Study PIs ([name], [name]) are blinded to the safety monitoring process which is led by the study biostatistician.

All deaths among individuals who have received the intervention from intervention clinics, and those who would have been eligible to receive the initial mailing from control clinics will be reviewed by a trained Pharm D chart abstractor to determine whether the death occurred within 4 months of a medication

adjustment by the patient's primary care physician. Similarly, every third hospitalization for these two groups will be reviewed to determine the primary diagnosis for that hospitalization and whether the potential serious adverse event occurred within 4 months of a medication adjustment by the patient's primary care physician. (The abstraction sample will be generated weekly.) The PharmD medical record abstractor, a member of the KPCO pharmacy department, will access the tracking database and will review each record using a chart abstraction tool. Records provided to the PharmD will not indicate intervention versus delayed control status but the PharmD cannot be fully blinded due to potential evidence in staff messages related to the study in some charts. In addition to avoiding study status identification on records sent to the PharmD, potential bias will be minimized by detailed chart data extraction steps to be consistently followed.

Throughout the study period any physician, pharmacist or health care staff member will be able to report concerns about a safety issue that arises via an email or phone call to the KPCO Project Manager or the KPCO PI. All clinician Tip Sheets will include contact information for the KPCO PI.

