### **5.4 Reporting procedures**

#### **Follow-up for Adverse Events Reported by Clinic Staff**

For any reports from clinic staff of PCPs, the KPCO PI will contact the PCP to review the potential concern and will refer the participant's record for chart abstraction as described above. All potential concerns will be noted and discussed with the DSMB at regular meetings (or immediately for any serious adverse event potentially due to the intervention) and will be reported to the KPCO IRB. Any serious adverse events likely to have resulted from the intervention will be reported to the KPCO IRB, the DSMB and NIA within 5 calendar days. Concerns unlikely to have resulted from the intervention will be summarized for routine DSMB reporting in a separate table prepared by the study biostatistician. Any Serious Adverse Event affecting immediate patient safety will be reported to the KPCO IRB, DSMB, and NIA within 24 hours by

one of the study PIs. Follow-up will extend until discharge from the hospital for hospitalizations or completion of any acute care services associated with an adverse event.

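### The chart review's stated question covers only medication adjustments by the primary care physician, although section 5.1 also names stopping by patients or care partners as a possible harm

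*Protocol*

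**What the plan says.** Protocol section 5.1 begins its list of possible unintended effects with "inadvertent stopping of necessary medications by patients or care partners and associated effects of those potential discontinuations". Further on, as a separate pathway, it names the harms that could follow a discontinuation agreed between the PCP and the patient or care partner.

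Section 5.2 sets out two main safety elements.

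- **Rates by arm.** "Every 3 months rates of hospitalizations, and mortality will be compared between groups who have received the intervention" and the corresponding control-clinic patients.
- **Chart abstraction.** All deaths and every third hospitalization are reviewed "to determine if the potential serious adverse event occurred within 4 months of a medication adjustment by the" patient's PCP. The criterion is then restated for deaths, which go to a trained "Pharm D chart abstractor to determine whether the death occurred within 4 months of a medication" adjustment by the PCP. It is restated again for sampled hospitalizations, where the abstractor is asked "to determine the primary diagnosis for that hospitalization and whether the potential serious adverse event occurred within 4 months of a medication" change made by the PCP. The next step is stated as follows: "Causality related to the medication adjustment will be reviewed in a blinded fashion by steering committee investigators".

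Section 5.2 adds that "any physician, pharmacist or health care staff member will be able to report concerns about a safety issue". Under section 5.4, the local principal investigator contacts the PCP about such a report and refers the participant's "record for chart abstraction as described above".

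**The concern.** The intervention reaches patients with dementia or mild cognitive impairment, and their care partners, directly by mail. A medicine could therefore be stopped by two routes: by the PCP after a discussion, or by the patient or care partner alone. Section 5.1 recognises both. The attribution step in section 5.2 asks about the first only.

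What is at stake is how the findings reported to the Data Safety Monitoring Board (DSMB) are read. A low count of events linked to a medication change would be a count of events linked to PCP changes. It could be taken as reassurance about the intervention as a whole, although the stated question did not cover the other route.

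**Working it through.** The protocol gives no figure on this point to reproduce. The main check is a reading of sections 5.1 and 5.2 together.

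**Step 1: follow an event through the plan as written.** Take a death or a sampled hospitalization.

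| In the prior 4 months | Stated screen | Stated causality question |
|---|---|---|
| PCP adjustment, no patient stop | Positive | In scope |
| PCP adjustment and patient stop | Positive | In scope for the adjustment; the stop may be noticed, but is not asked about |
| Patient or care-partner stop, no PCP adjustment | Negative | Out of scope |
| Neither | Negative | Out of scope |

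The third row is the gap. It cannot be told apart from the fourth, even when the chart documents the stop. For hospitalizations the reviewer also records the primary diagnosis, but that does not show who stopped a medicine.

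**Step 2: ask whether the rate comparison could stand in for the missing question.**

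Inputs from the protocol:
- 3,671 eligible members in 18 clinics, and about 80% expected to receive a mailing (section 7.2)
- baseline hospitalization rate of up to 30% (section 5.3)
- intraclass correlation (ICC) of 0.01, given for medication counts (section 7.2)

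Assumptions:
- the 80% applies to both arms
- the ICC carries over to hospitalization, with a range of 0.001 to 0.02
- equal clinic sizes, two-sided alpha of 0.05 and 80% power

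Calculation:
- Patients per arm: 3,671 × 0.8 / 2 ≈ 1,468. Per clinic: 3,671 × 0.8 / 18 ≈ 163.
- Design effect: 1 + (m − 1) × ICC = 1 + 162.2 × 0.01 ≈ 2.62.
- Effective number per arm: 1,468 / 2.62 ≈ 560.
- Smallest detectable excess over 30%, from a two-proportion comparison with 560 per arm: 7.95 percentage points. As a check, the standard error is √[(0.30 × 0.70 + 0.3795 × 0.6205) / 560] ≈ 0.0282, and 0.0795 / 0.0282 ≈ 2.82, close to 1.96 + 0.84 = 2.80.
- In patients: 0.0795 × 1,468 ≈ 117 extra hospitalized.

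| ICC | Design effect | Effective n per arm | Detectable excess (points) | Extra patients hospitalized |
|---|---|---|---|---|
| 0.001 | 1.16 | 1,264 | 5.25 | 77 |
| 0.01 | 2.62 | 560 | 7.95 | 117 |
| 0.02 | 4.24 | 346 | 10.15 | 149 |

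The rate comparison would reliably show only a large excess, and it does not attribute individual events.

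**The case against.** A reader might infer that the safety plan is blind to patient-initiated stopping, or that chart review has no sensitivity for it at all. The protocol does not support either reading, for these reasons.

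- **Mailings are tied to PCP visits.** The feasibility cohort had a median of 5 visits in the prior year (section 7.2). Some patients who stop a medicine will also have a PCP adjustment within 4 months, so their charts will be reviewed. No sensitivity figure can be derived.
- **The abstraction tool is not shown.** Section 5.2 refers to a tool and to detailed extraction steps, which may hold further items. The point concerns the question the protocol states.
- **The rate comparison counts serious events whoever stopped the medicine.** Because clinics are randomized, an excess in one arm would itself be evidence of an intervention effect. The protocol does not say whether the rates are adjusted.
- **There is a route that does not depend on the initiator.** Sections 5.4 and 7.3 send serious adverse events likely or potentially due to the intervention to the ethics board and the DSMB or its chair.
- **The mailing tells patients not to stop medicines without talking to their PCP** (section 2), and its cover letter gives study contacts.
- **Section 5.1 does not promise that chart review will attribute every harm it lists**, and coming first in a list does not imply priority.

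All of this stands as a limit on the point, but none of it closes the gap. The instruction in the mailing prevents harm and does not measure it. Staff reports are voluntary, and once made they go to the same abstraction. Section 5 describes no process for reports from patients or care partners.

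**Conclusion.** The point holds for the chart review as stated. Section 5.1 names a harm that the abstraction criterion in section 5.2, and the causality review linked to it, do not cover. A death or sampled hospitalization after a patient- or care-partner-initiated stop, with no PCP adjustment in the prior 4 months, would be recorded as negative.

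The number of such events cannot be estimated, because the protocol gives neither the frequency of patient-initiated stopping nor that of PCP adjustments. The only size available is for the backstop: a detectable excess in hospitalization of about 8 percentage points (5.3 to 10.2 across the ICC range), under the assumptions in the working.

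This is a worthwhile and inexpensive improvement to safety attribution. It does not show that the safety plan as a whole fails, and it does not touch the primary outcomes.

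**What to change.** Reword the abstraction question in section 5.2, in all three places, to cover any chart-documented stop or reduction of a chronic medication in the prior 4 months, including one made by the patient or care partner. Record who initiated it. Keep the existing item on PCP adjustments alongside, so that nothing now captured is lost. Send positives to the same blinded causality review in both arms, and report the findings to the DSMB by initiator.

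Dispensing data may be used to corroborate a documented stop. A refill gap alone should not trigger review: in patients on 5 or more chronic medicines, many gaps could be unrelated to any decision to stop.

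The cost is some added abstraction time on charts that the pharmacist already opens, and more cases for causality review. The protocol does not allow the increase to be quantified. If the abstraction tool already holds such an item, it is enough to say so in section 5.2 and to extend the causality question to it.
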